#### Moderators

Due to the lack of existing research in this field, the moderation analyses of main effects are exploratory and may investigate various moderators of intervention components, different forms of operationalizing these moderators, or varying types of relationships (eg, linear or quadratic). Moderations of main effects are investigated by adding a term for the interaction between the main effect and the respective moderator to the statistical model.

#### State of Receptivity

We will compare several different methodological approaches to predict the participants’ state of receptivity. First, we plan to evaluate the performance of supervised learning algorithms in predicting response rate and response time. These algorithms have produced predictions of acceptable accuracy in previous studies on interruptibility [58]. Second, we plan to frame the problem at hand as a classification problem. A classifier will be trained to learn to differentiate between contexts in which the notification is sent (and are assumed to represent nonreceptive contexts) and contexts in which the participant interacts with the app (and in turn are assumed to represent receptive contexts). To this end, we aim to use generalized linear models as a starting point before exploring online learning algorithms that can learn and adapt to each participant’s preferences, and any change thereof. This analysis strategy, however, is preliminary at the time of writing, as the final analysis will consider additional factors such as the quality and distribution of collected data.

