**Incentives**						
	Cash incentives	Upon enrollment; allocation ratio 1:1:1	Dashboard/chat	Daily	10.2	Overall proportion of participant days that step goals were achieved
	Charity incentives	Upon enrollment; allocation ratio 1:1:1	Dashboard/chat	Daily	10.3	Overall proportion of participant days that step goals were achieved
	Control (no incentives)	Upon enrollment; allocation ratio 1:1:	N/A	N/A	N/A	Overall proportion of participant days that step goals were achieved

^a^1.2=problem solving, 1.4=action planning, 1.6=discrepancy between current behavior and goal, 2.2=feedback on behavior, 4.1=instruction on how to perform a behavior, 10.2=material reward (behavior), and 10.3=nonspecific reward.

^b^N/A: not applicable

**Table 3 table3:** Summary of collected sensor data.

Sensor	Variable	Data type	Frequency^a^
GPS^b^	Location	3D Float	Every 10 min
Accelerometer	Physical activity	Categorical	Continuous
Time	Time	Integer	Continuous
Proximity	Proximity of the phone	Binary (near and far)	Continuous
Wi-Fi	Wi-Fi connection	Categorical/string	Every 10 min
Bluetooth	Bluetooth connection	Categorical/string	Every 10 min
Ambient light	Ambient light	Float	Continuous
Battery status	Battery status	Float (charged in percentage)	Continuous
Screen events	Screen on/off	Binary (on/off)	Continuous

^a^Estimated frequencies only. Actual frequencies may vary depending on device and operating system.

^b^GPS: global positioning system.

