#### Sensor Data

Drawing on previous literature on context-aware mobile notification management systems [58], we identified smartphone sensors that may aid with predicting the participants’ state of receptivity. Sensor data were obtained from participants during the intervention period. Table 3 provides a summary of these sensors, their collected data, and their sensing frequency. In line with previous studies, we operationalize state of receptivity by using the response rate (ie, whether a participant responds to a notification or not) and the response time (ie, time between notification and response) to notifications of the Ally app.

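### In the second receptivity classifier, the receptive class is defined by app use, so screen state read at that moment can inflate accuracy

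*Protocol article*

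**What the plan says.** The protocol article describes two approaches under State of Receptivity. The first is to "evaluate the performance of supervised learning algorithms in predicting response rate and response time". The second is a classifier with two classes. The nonreceptive class consists of "contexts in which the notification is sent (and are assumed to represent nonreceptive contexts"; the receptive class consists of "contexts in which the participant interacts with the app (and in turn are assumed to represent receptive contexts". The section ends with a caveat: "This analysis strategy, however, is preliminary at the time of writing".

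Under Sensor Data the authors state that "we identified smartphone sensors that may aid with predicting the participants’ state of receptivity" and point to Table 3 for the list. That table includes screen events (binary on/off), ambient light, and "Proximity of the phone", coded "Binary (near and far"; all three are listed as continuously sampled. The same section operationalises receptivity through the response rate, that is "whether a participant responds to a notification or not", and the time taken to respond.

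**The concern.** A participant cannot use the app with the screen off. In the receptive class, screen state read during use therefore takes a single value, and it does so because of the label. The nonreceptive class has no such constraint. Most notifications go out at random times within set windows (Study Design; Intervention Components), the evening feedback goes out at 8 pm, and dialogue times had to be known in advance (Randomization, Allocation Concealment, and Blinding), so sending does not depend on whether the screen is on. A classifier given this input can score well by recognising that the phone is in use now.

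The third objective is to predict receptivity, and the Introduction and the Discussion say that such predictions should inform when an intervention is delivered. That decision comes before any interaction. A predictor value produced by the interaction is not available then, and accuracy that rests on it does not carry over. The section also plans to compare approaches, and inflated accuracy in one of them would distort that comparison.

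**Working it through.** The protocol gives no accuracy, power or sample-size figure for the receptivity models, so there is no stated figure to reproduce. The calculations below show the size of the effect under stated assumptions.

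**Inputs**
- P(screen on | app interaction) = 1, from the class definition.
- P(screen on | notification sent) = q. The protocol does not give q; it is assumed to lie between 0.10 and 0.40, with 0.50 added in the simulation.
- Answering is unrelated to every sensor, so there is no true signal to find.

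**Screen-only rule.** Predict receptive when the screen is on. Sensitivity is 1 and specificity is 1 − q. For one binary predictor, AUC equals balanced accuracy: (1 + 1 − q)/2 = 1 − q/2.

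| q | AUC |
|---|---|
| 0.10 | 0.95 |
| 0.20 | 0.90 |
| 0.30 | 0.85 |
| 0.40 | 0.80 |

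**Same data, protocol's definition of receptivity.** A simulation of 20,000 notifications, half of them answered independently of context, compares the second classifier's labels with answered/not answered predicted from the screen state at sending.

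| q | Second classifier's labels | Answered or not, from sending context |
|---|---|---|
| 0.10 | 0.951 | 0.500 |
| 0.30 | 0.850 | 0.498 |
| 0.50 | 0.750 | 0.504 |

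**Proximity.** Suppose the phone reads far during all app use (an assumption, since the label does not fix it) and far at sending with probability f. The AUC is 1 − f/2: 0.85, 0.75, 0.65 and 0.55 for f = 0.3, 0.5, 0.7 and 0.9. The leak can be strong or almost absent. Ambient light was not quantified.

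**Device-use sensors left out, true signal elsewhere.** Let a binary sensor such as location be evenly split, unchanged between sending and answering, and let it shift the answer probability to 0.5 + d or 0.5 − d.
- Second classifier: sensitivity 0.5 + d, specificity 0.5, balanced accuracy 0.5 + d/2.
- Answer predicted from sending context: sensitivity and specificity both 0.5 + d, balanced accuracy 0.5 + d.

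For d = 0.1, 0.2 and 0.3 the formulas give 0.55, 0.60 and 0.65 for the second classifier, against 0.60, 0.70 and 0.80. Simulation gave 0.551, 0.599 and 0.645, against 0.601, 0.700 and 0.792. The second classifier retains a real signal, but a weaker one, because answered notifications also count as nonreceptive at sending.

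**The case against.** The strongest reply is that the leak is inferred. The section names neither the predictors of the second classifier nor the instant at which they are read. Table 3 summarises what was collected, and the text says only that the sensors may help. Feature extraction is the kind of detail a condensed article leaves to a fuller plan, Multimedia Appendix 2 is not shown, and the strategy is declared preliminary. Screen state before an event is also legitimate context that a future app could read.

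Part of this stands. Reading the listed sensors at the interaction is the natural interpretation, not an explicit statement, so the conclusion has to be conditional. But the point is not a missing detail: the class contrast is stated, and applied to the listed sensors it produces the leak. The caveat gives data quality and distribution as examples of what may change the strategy and does not mention predictor timing. Screen state that precedes the interaction can stay; only values generated by the interaction are at issue.

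A reader might go further and infer that proximity also separates the classes by construction, that the classifier's accuracy says nothing about receptivity, or that this approach would win the comparison. The documents support none of these. Only screen state is fixed by the label. Other sensors can carry a diluted signal, as the last calculation shows. The section states no comparison metric or selection rule, so all one can say is that the approach could look better than it is.

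**Conclusion.** The point holds in conditional form. If screen state at the moment of app use enters the second classifier, its accuracy is inflated by the label and cannot be read as receptivity as the Sensor Data section defines it, nor set beside the first approach at face value. With an assumed screen-on rate of 10% to 40% at sending, the screen alone yields an AUC of 0.95 to 0.80 with no true signal. That range is illustrative and depends entirely on q. Any contribution from proximity or ambient light is of unknown size.

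The scope is limited to one of the approaches within an exploratory secondary objective. The first approach and the primary analyses are not affected. It is still worth correcting, because Expected Results and Dissemination places the data analyses after publication of the protocol and the change needs only analysis code.

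**What to change.** 1. In the second classifier, either exclude screen, proximity and ambient-light values from both classes, or use only values recorded before the session's screen-on event and, for answered notifications, no later than the sending time. Exclusion is simpler. Under the second option, screen use should enter as a summary over a preceding stretch of time, because the last state before a screen-on event is off by definition.
2. Report the accuracy of a screen-only model as a benchmark.
3. Judge both approaches on the same test: predictions from context at sending, scored against answered/not answered and response time. This step matters most, because step 1 removes the leak but leaves the diluted label in place.

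A fixed lag before the session, such as the 5 minutes the protocol uses to separate sessions, is a poor substitute. For a notification answered within 5 minutes, the window closes before the notification was sent, so nearly the same context carries both labels. GPS, Wi-Fi and Bluetooth are also sampled only about every 10 minutes.

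The cost is feature-extraction code and a sentence or two in the analysis plan, with no new data. Reported accuracy will probably be lower, and some sessions will be lost for lack of earlier sensor records.

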## Results

### Recruitment

Of all 30,000 invited insurees, 749 (2.50%) clicked the link in the invitation mail and were subsequently screened for eligibility. Of those, 694 (92.7%) were eligible and 382 (51.0%) provided informed consent to participate. Of all insurees who provided informed consent, 274 (71.7%) successfully completed the baseline survey and installed the Ally app on their smartphone (Figure 3). Invited insurees were given the opportunity to select reasons why they declined participation from a list of predefined answer options using a separate survey (n=191). A link to this survey was included in the invitation mail and placed on the informed consent screen. Possession of an incompatible smartphone (37/191, 19.4%) and unwillingness to share smartphone sensor data (35/191, 18.3%) were the most frequently stated reasons to decline participation.

Of 274 participants, 32 (11.7%) did not receive any interventions because they stopped using the app before the start of the intervention period. Due to technical errors, 6 participants did not receive the interventions they were randomized to (eg, a self-monitoring prompt was sent out on a day where the participant was randomized to not receiving a prompt). For the 6 participants, these errors affected between 1 and 25 out of 42 participant days. Steps per day measured with the smartphone are available for 227 (82.8%, 227/274) participants, and smartphone sensor data are available for 247 (90.1%, 247/274) participants. After completing the 6-week intervention period, 181 (66.1%, 181/274) participants filled out the Web-based follow-up survey. Data collection finished in January 2018.

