For financial and charity incentives, postintervention differences in intrinsic and extrinsic motivation, and differences in app engagement and nonusage attrition during the intervention period are evaluated as additional secondary outcomes. Dimensions of intrinsic and extrinsic motivation are measured using the Behavioral Regulation for Exercise Questionnaire-2 (BREQ-2) [46]. As the external regulation subscale in the BREQ-2 exclusively relates to external regulation by other people, it is substituted by the more generally worded external regulation subscale of the Situational Motivation Scale (SIMS) [47]. Subscales of both instruments have shown good reliability (Cronbach alpha=.73-.86, BREQ-2 [46] and Cronbach alpha=.86, SIMS external regulation subscale [47]). Validity has been confirmed by factor analysis (BREQ-2) [46] and correlational analysis (SIMS) [47]. We measure engagement with the Ally app using the number and length of app launch sessions per day. An app launch session is defined as any interaction of the participant with the Ally app, separated by 5 min between events. If a participant left the app open and did not take action for 5 min or more, then the next interaction with the app counts as a new session. We coded a participant as “non-usage attrition observed” when she/he stopped using the Ally app at least 7 days before the end of the study.

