#### Primary Analyses

To evaluate main effects and interactions of intervention components, we will use the centered and weighted GEE approach described in the study by Boruvka et al [62]. This approach guarantees unbiased effect estimates when treatment and moderator variables are time-varying. Statistical models will evaluate each main effect and interaction of intervention components of interest on the components appropriate proximal outcome. For all main effects and interactions that include comparisons of multiple conditions, the main comparisons of interest are between the respective intervention and control conditions.

Missing data on covariates and on the dependent variable will be imputed using multiple imputation, provided the missing at random assumption is justified. We will perform sensitivity analyses to assess the robustness of the results of the primary analyses. These analyses include a per-protocol analysis and an adjusted analysis in which effect estimates are adjusted for a linear trend of time, baseline step count, and covariates of physical activity. For all tests, we use 2-sided *P* values with alpha<.05 level of significance.

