#### Secondary Analyses

Secondary analyses focus on the analysis of intervention components on participants’ step counts and on the effects of incentives on app engagement, nonusage attrition, and motivation. Steps per day are analyzed using the same modeling approach as described above. Again, if missing data can be assumed to be missing at random, we plan to impute missing step counts using multiple imputations. As evidence suggests that participant days with less than 1000 steps are unlikely to represent accurate activity data [63,64], those days will be set to missing before imputation.

Generalized linear models will be used to analyze the effect of incentives on engagement and nonusage attrition. One-way analysis of variance (ANOVA) is performed for each subscale of the BREQ-2 to analyze the effect of incentives on the different forms of intrinsic and extrinsic motivation. *P* values will be adjusted according to the Holm-Bonferroni method [65]. If the omnibus test of the ANOVA is significant, we will investigate contrasts between the 3 incentive groups. Again, the main comparison of interest is between the intervention groups and the control group. An overview of all planned statistical analysis is available in Multimedia Appendix 2.

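### As stated, the motivation ANOVA uses by default only the 66% who returned the follow-up survey; if return depends on incentive arm and on motivation, the arm contrasts can be biased

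*Protocol article*

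**What the plan says.** Under Primary and Secondary Outcomes, the article lists for the incentive component that "postintervention differences in intrinsic and extrinsic motivation, and differences in app engagement and nonusage attrition during the intervention period are evaluated as additional secondary outcomes". Motivation is measured with the BREQ-2, with its external regulation subscale replaced by that of the SIMS.

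Under Secondary Analyses the method is "One-way analysis of variance (ANOVA) is performed for each subscale of the BREQ-2 to analyze the effect of incentives" on the forms of motivation. P values are Holm-Bonferroni adjusted, and contrasts between arms follow only if the omnibus test is significant. No missing-data rule is attached to this analysis.

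Missing-data rules are given elsewhere:
- Primary Analyses: "Missing data on covariates and on the dependent variable will be imputed using multiple imputation, provided the missing at random assumption is justified".
- Secondary Analyses, for steps: "if missing data can be assumed to be missing at random, we plan to impute missing step counts using multiple imputations".

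Under Results, Recruitment, the article reports that after the intervention period "181 (66.1%, 181/274) participants filled out the Web-based follow-up survey". It also reports that 32 of 274 stopped using the app before the intervention period began.

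**The concern.** A one-way ANOVA of a post-intervention score drops everyone without that score. Here that is a third of the enrolled participants, and the randomised comparison becomes a comparison of responders.

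That is harmless if non-return is unrelated to motivation, or if its rate and its relation to motivation are the same in every arm. Neither can be taken for granted. The trial itself tests whether incentives change how long people keep using the app, so it treats retention by arm as an open question. It is also plausible that people who lose interest are less likely to answer a final questionnaire.

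At stake is the comparison that bears on the worry, raised in the Incentives subsection of Intervention Components, that payment may lower intrinsic motivation. Suppose responders are the more motivated and unpaid participants return the survey less often. The unpaid arm's observed mean is then pushed up more than the paid arms' means, which would imitate such a loss. If the return rates run the other way, a real loss could be hidden.

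**Working it through.** **1. The article's own figure.** 181/274 = 0.6606, which matches the stated 66.1%. Missing: 274 − 181 = 93, and 93/274 = 33.9%. No power or sample size is stated for motivation, so there is none to reproduce.

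**2. How much of the loss could fall after exposure.** 274 − 32 = 242 reached the intervention period. The overlap between the 32 early leavers and the 93 non-returners is not stated. If all 32 are among the 93, then 93 − 32 = 61 of 242 (25.2%) were lost after reaching the intervention period, and return in that group is 181/242 = 74.8%. If all 32 did return the survey, return in that group is 149/242 = 61.6%.

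**3. Loss of precision.** With 1:1:1 allocation, about 274/3 = 91 are randomised per arm and, if return is even, 181/3 = 60 are analysed. The difference detectable with 80% power in one pairwise contrast is (1.96 + 0.84) × √(2/n): 0.41 SD at 91 per arm and 0.51 SD at 60.

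**4. Bias formula.** Let r be the return rate in an arm and g the mean motivation of responders minus that of non-responders, in SD units, equal in both arms. The responder mean exceeds the full-arm mean by (1 − r) × g. With no true effect, the size of the bias in a contrast is |r1 − r2| × g, and the standard error is √(1/(91 r1) + 1/(91 r2)). The rejection rate at two-sided 5% is 1 − Φ(1.96 − b/SE) + Φ(−1.96 − b/SE).

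Neither return by arm nor g is in the article. Both are assumptions, chosen to average about 66% return.

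| Assumed return | g (SD) | Bias (SD) | SE | Rejection, one contrast |
|---|---|---|---|---|
| 76% vs 56% | 0.5 | 0.20 × 0.5 = 0.10 | 0.185 | 8.4% |
| 76% vs 56% | 0.8 | 0.20 × 0.8 = 0.16 | 0.185 | 13.9% |
| 73% vs 60% | 0.5 | 0.13 × 0.5 = 0.065 | 0.183 | 6.5% |
| 73% vs 60% | 0.8 | 0.13 × 0.8 = 0.104 | 0.183 | 8.8% |
| 66% vs 66% | any, same in both | 0 | 0.182 | 5.0% |

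**5. A second selection model.** Let return follow a latent normal variable with correlation ρ to motivation, so that the responder mean is ρ φ(c)/r with c = Φ⁻¹(1 − r). For 76% vs 56% and ρ from 0.2 to 0.5, bias is 0.06 to 0.15 SD and rejection 6.2% to 12.6%, the same order as above. Equal return rates do not protect by themselves: at 66% in both arms, with selection in one arm only, bias is 0.17 SD (ρ = 0.3, rejection 15%) to 0.28 SD (ρ = 0.5, 33%).

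**6. With the omnibus gate.** The rates above are for one ungated contrast. Simulating three arms at 76%, 66% and 56% with the step 4 gaps, and counting the extreme contrast only when the 5% omnibus test is also significant, gives 4.6% to 8.2%, against 2.5% with no bias. For 73%, 66% and 60% it is 3.4% to 4.8%. The Holm adjustment lowers these further.

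**The case against.** **The article is silent rather than wrong.** It never says that only complete cases are analysed, and Multimedia Appendix 2, which lists the planned analyses, is not shown. This stands as a limit: responder-only is the default reading, not a stated rule. It does not remove the point, because the article gives missing-data rules for the primary analyses and for steps, then specifies the motivation analysis down to the multiplicity method without one.

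**Two kinds of drop-out differ.** The attrition that the trial tests is stopping app use at least 7 days before study end. What matters here is return of a web survey, and completing both questionnaires earns CHF 10, with no difference by arm described. This stands. A reader might infer that the trial's interest in attrition shows survey return to depend on arm. It shows only that app retention by arm is an open question, and the two are related but not the same.

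**Early leavers.** Up to 32 of the 93 stopped using the app before any intervention, so that part of the loss is unlikely to be caused by incentives. This stands, but at least 61 non-returners remain.

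**The size is assumed.** This also stands. In the step 4 scenarios the bias is below one standard error, and the omnibus gate and Holm adjustment reduce the rejection rates.

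**Imputation is only a partial remedy.** If people fail to reply because of the motivation that was not observed, imputation under missing at random corrects only what the observed data explain. Step data exist for only 227 of 274, and the article does not expressly say that motivation was measured at baseline. The article also makes imputation conditional on missing at random being justified. These points shape the fix and do not argue for leaving the responder-only analysis as the main one.

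**Conclusion.** The point holds as a conditional one. As stated, the motivation comparison by default uses 181 of 274 participants, and its contrasts can be biased if survey return differs by incentive arm and is related to motivation, or if that relation differs between arms.

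A reader might go further and conclude that the contrasts are biased, or that the bias favours one arm. The article does not support either: it gives no return by arm and no information on how non-responders differ. The bias of 0.10 to 0.16 SD, with 8% to 14% rejection for a single contrast before gate and Holm, rests on assumed return of 76% versus 56% and an assumed gap of 0.5 to 0.8 SD. It is zero when return and its relation to motivation are the same in all arms.

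This concerns a secondary outcome. The primary step-goal analysis has its own stated imputation plan and sensitivity analyses. It is a cheap improvement, and the article says that data analyses start only after its publication.

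**What to change.** - Extend the already planned multiple imputation to the motivation subscales. Include in the imputation model the incentive arm, baseline questionnaire data (with baseline motivation if it was measured), app sessions, last day of use, and goal attainment where available.
- Keep the responder-only ANOVA as a sensitivity analysis.
- Report follow-up survey return by incentive arm.
- Add one delta-shift analysis, in which imputed scores of non-responders are moved by a stated amount, allowed to differ by arm, to show how large a departure from missing at random would change the conclusion.

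The cost is a little more analysis and possibly slightly wider intervals. No new data are needed.
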